## Abstract

**Background:**

Vertebroplasty is a promising but as yet unproven treatment for painful osteoporotic vertebral fractures. It involves radiographic-guided injection of various types of bone cement directly into the vertebral fracture site. Uncontrolled studies and two controlled quasi-experimental before-after studies comparing volunteers who were offered treatment to those who refused it, have suggested an early benefit including rapid pain relief and improved function. Conversely, several uncontrolled studies and one of the controlled before-after studies have also suggested that vertebroplasty may increase the risk of subsequent vertebral fractures, particularly in vertebrae adjacent to treated levels or if cement leakage into the adjacent disc has occurred. As yet, there are no completed randomised controlled trials of vertebroplasty for osteoporotic vertebral fractures. The aims of this participant and outcome assessor-blinded randomised placebo-controlled trial are to i) determine the short-term efficacy and safety (3 months) of vertebroplasty for alleviating pain and improving function for painful osteoporotic vertebral fractures; and ii) determine its medium to longer-term efficacy and safety, particularly the risk of further fracture over 2 years.

**Design:**

A double-blind randomised controlled trial of 200 participants with one or two recent painful osteoporotic vertebral fractures. Participants will be stratified by duration of symptoms (< and ≥ 6 weeks), gender and treating radiologist and randomly allocated to either the treatment or placebo. Outcomes will be assessed at baseline, 1 week, 1, 3, 6, 12 and 24 months. Outcome measures include overall, night and rest pain on 10 cm visual analogue scales, quality of life measured by the Assessment of Quality of Life, Osteoporosis Quality of Life and EQ-5D questionnaires; participant perceived recovery on a 7-point ordinal scale ranging from 'a great deal worse' to 'a great deal better'; disability measured by the Roland-Morris Disability Questionnaire; timed 'Up and Go' test; and adverse effects. The presence of new fractures will be assessed by radiographs of the thoracic and lumbar spine performed at 12 and 24 months.

**Discussion:**

The results of this trial will be of major international importance and findings will be immediately translatable into clinical practice.

**Trial registration:**

Australian Clinical Trial Register # [ACTRN012605000079640]

## Background

Vertebral fractures are the most common form of osteoporotic fracture and yet are often an under-recognised cause of morbidity and perhaps mortality in our community [1,2]. Apart from analgesia, bed rest and physical therapy, all of which may be of value, there are no effective interventions. While calcitonin has been demonstrated to have an analgesic effecin two placebo-controlled studies [3,4], it is not registered for use for this purpose in Australia. Interventions that effectively manage the pain, shorten the recovery time and eliminate the need for extended nursing and rehabilitation care would be of great value to both reduce the personal burden borne by those affected, and reduce the high management costs.

Vertebroplasty is a promising but as yet unproven new treatment for painful osteoporotic vertebral fractures [5]. It was first developed in France in the late 1980s to treat spinal hemangiomas and subsequently osteolytic metastases and myeloma [6]. It involves percutaneous injection of poly-methyl methacrylate (PMMA) or a like material, opacified with barium sulfate into the involved vertebral body under fluoroscopic and/or CT guidance. Injection of 2–4 millilitres of cement (combined with a radio-opaque substance such as barium) via a transpedicular approach is usually performed under local anaesthesia combined with neurolept analgesia and may be done as an outpatient procedure or in a short hospital stay. The mechanism of pain relief with vertebroplasty is not known. Theories include thermal or chemical local effects on nerve endings, and a mechanical effect of stabilization of an unstable (ie. moveable) fracture [7]. The semisolid mixture of PMMA has been shown to restore strength and stiffness of vertebral bodies in post-mortem studies [7].

Since 1994, there have been numerous published case reports and case series ranging from 1 to 260 patients, treated for painful osteoporotic spinal fractures [8-16]. In these retrospective and uncontrolled prospective reports, vertebroplasty has been associated with an often immediate, dramatic and sustained improvement in pain and increased mobility in most patients. However uncontrolled studies tend to overestimate treatment benefit for a variety of reasons [17]. They fail to take into account the natural history of the condition which is to improve over time; they make no allowance for the statistical artefact of 'regression to the mean'; and do not adjust for the placebo response which is likely to be accentuated with an invasive procedure [18].

Two recent quasi-experimental controlled before-after studies that compared volunteers who were offered treatment to those who refused it, have also suggested an early benefit of vertebroplasty in terms of rapid pain relief and improved function [19,20]. However, these study designs are vulnerable to substantial bias. Volunteers may have a better outcome than those who decline to receive a new therapy as a function of self-selection. In one study, those who agreed were more disabled at baseline and so had greater potential to improve [20]; while participants in the other study were treated early in the course of the condition and most were treated as inpatients, so the results may not pertain to patients who have had pain for longer than a few weeks [19].

In general, the risk of subsequent vertebral fracture once a vertebral fracture has occurred is very high – for example, the risk within a year of a single vertebral fracture has been estimated to be ~20% in those with untreated osteoporosis and ~10% in those treated with bisphosphonates [21]. Several recent uncontrolled studies have suggested an increased incidence of subsequent vertebral fractures with vertebroplasty, particularly in vertebrae adjacent to treated levels or if cement leakage into the adjacent disc has occurred [22,23], while two controlled before-after studies have yielded conflicting results [19,20]. A possible increased risk of fracture in adjacent vertebrae may be due to an alteration in the distribution of biomechanical loading [24] and/or negative effects on bone remodelling (local acceleration of bone resorption) as a result of the treatment itself or a cytokine-mediated foreign-body reaction at the cement-bone interface [25]. Treated vertebrae have been found to be stronger and stiffer after vertebroplasty compared to osteoporotic bone [26,27].

Vertebroplasty may be of immense value but its potential benefits need to be weighed up with its potential risks. It is essential to quantify any increased risk of further vertebral fractures following vertebroplasty compared with conservative care and to determine whether there are any strategies that can minimise the risk. This study will determine the efficacy and safety of vertebroplasty for acute painful osteoporotic vertebral fracture compared with placebo in a randomised participant-blinded and outcome assessor-blinded trial. It will quantify the risk of developing new vertebral fractures in the first and second year following vertebroplasty in comparison to conservative care.

### Aims

The aims of this randomised placebo-controlled trial are to:

i) determine the short-term efficacy and safety (3 months) of vertebroplasty for alleviating pain and improving function for painful osteoporotic vertebral fractures; and

ii) determine its medium to longer-term efficacy and safety, particularly the excess risk of further fracture over 2 years.

## Methods

### Trial design

This is a participant and outcome assessor-blinded multicentre randomised placebo-controlled trial with 2-year follow-up (Figure 1).

**Figure 1 F1:**
[figure not shown]
Diagram of Recruitment and Participation Process.

### Ethics

Ethics approval has been received from the Human Research Ethics Committees of Monash University, Cabrini Health, Melbourne Health, Western Health, Southern Health, Northern Health, and the Alfred Hospital, all in Melbourne, Australia.

### Participants

Participants will be recruited from general practitioners, specialists who manage acute osteoporotic vertebral fractures and hospital inpatient and emergency departments. To increase awareness of the trial, we will advertise in local media, include regular updates in relevant medical organisation newsletters, and send regular newsletters to our referral base.

All potential participants will be screened to determine eligibility according to the following inclusion and exclusion criteria. Participants will have back pain of no more than 12 months duration. Osteoporotic spinal fractures will be confirmed by thoracic and lumbar spine radiograph and, if not already obtained, all participants (unless contraindicated) will have an MRI examination of the thoracic and lumbar spine to determine the position, extent, age and stability of the vertebral fracture and to ensure no exclusion criteria exist. Only participants with one or two recent vertebral fractures, defined as vertebral collapse and oedema or fracture line within the vertebral body, will be included. When an MRI is unable to be performed, a CT scan, to determine the position and extent of the vertebral fracture/s, and bone scan, to determine the presence of increased uptake in a distribution compatible with recent vertebral fracture will be required.

Exclusion criteria will be: the presence of more than two recent spinal fractures; presence of malignant disease in the spine; neurological complications; osteoporotic vertebral collapse of > 90%; fracture through or destruction of posterior wall; retropulsed bony fragment or bony fragments impinging on the spinal cord; discitis; osteomyelitis; uncontrolled sepsis; non-correctable coagulation disorder; medical conditions that make the patient ineligible for emergency decompressive surgery should it be necessary to treat a procedure complication (e.g. severe heart and/or lung disease, renal failure); current malignancy; dementia; previous vertebroplasty; inability to give informed consent; an/or likelihood of non-compliance with follow up.

### Randomisation

Participants who fulfil inclusion criteria and consent to take part in the trial will be randomised in permuted blocks of 4 and 6, stratified by treating radiologist, gender and duration of symptoms (< 6 weeks versus = 6 weeks), to receive either the active or placebo regimen according to a computer-generated table of random numbers created by the study biostatistician. To ensure treatment allocation concealment, just prior to the procedure the treating radiologist contacts a central receptionist who provides the appropriate opaque sealed envelope containing the treatment allocation of the participant according to their identification number. Only the telephone receptionist has access to the allocation schedule and she has no other role in the trial.

### Interventions

All procedures will be standardised across sites. Patients will be positioned prone on the angiographic table and preliminary screening will be performed to identify the fracture level. A 25G intravenous cannula will be inserted into the dorsum of the hand or forearm and neurolept sedation/analgesia of midazolam and fentanyl (doses appropriate for weight and height) will be given as required during the procedure by the radiologist performing the procedure. A cardiac monitor clip will be placed on the other hand. For all patients, the skin will be prepared with an iodine-based solution and a drape will be placed over the body. All procedures will be standardised with care taken to preserve blinding in the event that patients do not have total amnesia. Throughout the procedure, blood pressure, heart rate, oxygen saturation and neurological status will be monitored. Procedures will be performed in hospitals with neurosurgical or orthopaedic surgical support in case of unforeseen complications and patients will be monitored for 4 hours following the procedure in the Day Procedure Ward prior to being discharged. Analgesia as required will be given following the procedure.

#### Percutaneous Vertebroplasty

The left pedicle of the fracture site will be identified with a metallic marker and a 25G needle will be used to infiltrate the skin overlying the pedicle. A longer 23G needle will be used to infiltrate the periosteum of the posterior lamina. A scalpel will be used to make a small incision in the skin. A 13G needle (Cook, USA) with a bevelled edge will be placed posterolateral relative to the eye of the pedicle. Gentle tapping using a hammer will be performed to guide the needle through the pedicle down into the anterior two thirds of the fractured vertebral body. Bi-plane imaging if available will guide needle placement, alternatively the image intensifier screen will be rotated from the A-P to the transverse planes and back again to monitor the progress of the needle as it passes through the bone. Both A-P and lateral images will be recorded with the needle in the correct position. Intravertebral contrast injection venography will be optional. Some operators find the localisation of veins to be useful. Ten ml dilute contrast will be injected through connecting tubing into the needle to assess filling of epidural veins with digital subtraction radiography if venography is used.

At the nursing trolley, the pre-packaged PMMA with radio-opacifier will be mixed to an appropriate consistency. This will be poured into a 20 ml syringe from which several 1 ml syringes will be filled. The stylet will be removed from the 13G needle transfixed within the vertebral body and approximately 3–4 millilitres PMMA will slowly be injected into the vertebral body rotating the needle in order to direct the passage of bone cement to the affected area. The working time for the injection is approximately 2 minutes. Having confirmed satisfactory infiltration of the vertebral body with bone cement in both A-P and lateral planes (with the image intensifier), the needle will be slowly removed by rotation. A unilateral approach will be used unless there is inadequate instillation of cement, in which case a bipedicular approach will be used. Extreme care will be taken to ensure that no leakage of cement occurs either into a vein or outside the bone. The injection will be stopped when significant resistance is met, or when the cement reaches the posterior quarter of the vertebral body or when there is escape into extraosseous structures or veins. All patients in the active group will receive 1 gram cephalothin IV as prophylaxis against infection.

#### Placebo treatment

Many patients who undergo vertebroplasty recall the tapping sensation against the vertebra. For this reason, subjects assigned to placebo will undergo the same procedures to insertion of the 13G needle to rest on the lamina. At that point, the central sharp stylet will be removed and replaced by a blunt ended stylet. To simulate vertebroplasty, gentle tapping with a hammer will be performed sufficient to generate enough noise and vibration to be heard and felt by the patient. The blunt ended stylet will be less likely to penetrate the bone during tapping with a hammer. At regular intervals the image intensifier will be rotated into the lateral planes and then back to the AP plane. At the nursing trolley, some PMMA will be reconstituted with barium and saline such that the smell permeates throughout the room. Several 1 ml syringes will be filled as for the active group and injection will be simulated.

All participants receive usual care according to the discretion of their treating doctor. Analgesia use is unrestricted and its use will be recorded at baseline and follow up. All treating physicians receive an information sheet about the trial as well as a copy of the most up-to-date guidelines for management of osteoporosis. Management of osteoporosis is at the discretion of the participants' treating physicians.

### Outcome Assessment

The same blinded assessor will assess all participants at baseline. Baseline data will include gender, date of birth, height, weight, risk factors for osteoporosis including use of certain medications such as corticosteroids and anticonvulsants, smoking and alcohol use, medications for osteoporosis, usual level of exercise, fracture history, current therapy for vertebral fracture. If not already available, plain films of the thoracic and lumbosacral spine will be obtained. If not performed within the previous year, bone mineral density measurement will also be performed.

All participants will be evaluated after the procedure at 1 week, 1, 3, 6, 12 and 24 months using mailed questionnaires. Reply-paid envelopes will be provided to maximise response rates.

The following outcomes will be assessed at each time point:

Overall pain, pain at rest, and pain in bed at night (over the last week) will be measured on a 0–10 numerical scale comprising a vertical line labelled "no pain" at the bottom (0) and "maximal imaginable pain" at the top (10) [28].

A range of standardised, self-report quality of life measures will be used:

The Assessment of Quality of Life (AQoL) is a health-related quality of life instrument comprising 15 items in 5 dimensions (Illness, Independent Living, Social Relationships, Physical Senses, and Psychological Well-being) [29,30]. It is well validated, responds to rapid changes in health status and is sensitive to changes in the frail elderly [29]. The AQoL incorporates utility weights that have been derived from an Australian population sample using time-trade off (TTO). The range of scores is between 0.00 (death) and 1.00 (perfect health), with higher scores representing better health-related quality of life. The utility score can be used in cost-utility analyses and calculation of Quality-Adjusted Life Years.

The quality of life questionnaire of the European Foundation for Osteoporosis (QUALEFFO) is an osteoporosis-specific measure comprising 41 items organised in five domains (Pain, Physical Function, Social Function, General Health Perception and Mental Function) [31]. Each domain score and QUALEFFO total scores are expressed on a 100-point scale, with lower scores corresponding to better health-related quality of life. It has demonstrated reliability between patients with and without vertebral fracture and QUALEFFO scores have been shown to increase progressively with increasing numbers of vertebral fractures [32].

The EQ-5D is a standard general quality of life instrument, measuring five domains (Mobility, Self Care, Usual Activities, Pain/Discomfort and Anxiety/Depression), with three levels in each, ranging in severity from no problem, some problem to extreme problem [33]. Respondents are then classified into one of 243 (3^5^) health states, with the best imaginable health state representing someone who reports the highest level of functioning in each domain. This instrument has been used in studies of patients with and without vertebral fractures [34,35].

The Roland Morris Disability questionnaire measures physical disability due to low back pain [36] but has also been shown to be an effective tool in evaluating vertebroplasty outcomes [37]. The original questionnaire consisted of 24 questions and was derived from the Sickness Impact Profile (SIP), with qualification 'because of my back pain' added to each question [36]. We will use a modified version comprising 28 items, modified to reduce the redundancy of some of the questions and to add items that better reflect changes in the patient [37]. Items are scored from 0 (no disability) to 28 (maximum disability). An additional question regarding the use of wheelchairs has been added and is scaled from 1 (no disability) to 4 (maximum disability).

Participants' perceived recovery with respect to pain, fatigue and overall health will be measured on 7-point ordinal scales ranging from 'a great deal worse' to 'a great deal better' at all follow up time points. It will be used to classify participants with a successful outcome, defined as 'moderately better' or ''a great deal better' across each indicator.

At baseline, 12 and 24 months, all participants will be assessed by the same blinded assessor who will administer the timed 'Up and Go' test [38]. This measures the time it takes a person to rise from a standard arm chair, walk to a line on the floor 3 metres away, turn around, return to the chair and sit down again. It is a widely used functional measure in older people and has good reliability and validity.

To determine the incidence of new vertebral fractures radiologically, all participants will undergo plain film examination of the thoracic and lumbosacral spine at 12 and 24 months. Regular serial follow-up films are recommended standard care following vertebroplasty to evaluate the treated vertebrae and to look for fractures in untreated vertebrae [25]. Two independent blinded radiologists will read the radiographs using the well-validated and reliable Genant semi quantitative method for identifying and gauging the severity of the fracture [39]. A new vertebral fracture will be defined as an increase in deformity grade (equivalent to a decrease of >15% in any vertebral height) from the baseline radiograph to the end of the study; or a new fracture in an existing prevalent fracture if there is progression to a higher grade of deformity (equivalent to a further vertebral height reduction of >15%) [39].

Success of blinding will be assessed at the end of the study by asking participants to indicate their treatment group. Five response options will range from 'I am definitely in placebo group', through to 'I am definitely in the vertebroplasty group', with 'don't know' as the central option.

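### The fracture readers are called blinded, but radio-opaque cement in one arm only lets a patient's follow-up films reveal the allocation

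*Protocol article*

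**What the plan says.** Under Trial design, the article describes the trial as blinded for participants and outcome assessors. Under Outcome Assessment, new fractures are found on plain films: "all participants will undergo plain film examination of the thoracic and lumbosacral spine at 12 and 24 months". The films are graded as follows: "Two independent blinded radiologists will read the radiographs using the well-validated and reliable Genant semi quantitative method". A new fracture is a rise in deformity grade from the baseline film. Progression of an already fractured vertebra to a higher grade also counts, so the treated level is part of the outcome.

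Under Percutaneous Vertebroplasty, "the pre-packaged PMMA with radio-opacifier will be mixed to an appropriate consistency", and then "approximately 3–4 millilitres PMMA will slowly be injected into the vertebral body". The Background describes the material used in this technique as "opacified with barium sulfate into the involved vertebral body under fluoroscopic and/or CT guidance".

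Under Placebo treatment, "subjects assigned to placebo will undergo the same procedures to insertion of the 13G needle to rest on the lamina", and later "Several 1 ml syringes will be filled as for the active group and injection will be simulated". No cement is left in the patient.

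The only check on blinding in the article asks participants, at the end of the study, which group they think they were in. Nothing comparable is described for the film readers.

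**The concern.** The cement is made to be visible on X-ray, it stays in the vertebra, and it is present in one arm only. Follow-up films of the thoracic and lumbosacral spine cover the region where it lies. A reader looking at a patient's set will usually be able to tell who was cemented, whatever is withheld on paper.

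This matters because the outcome involves judgement. The grading is semi-quantitative, so borderline grades leave room for the reader. The Background raises the suspicion of extra fractures next to treated levels or where cement has leaked into the disc. A reader who sees cement may thus know both the arm and the hypothesis. Any resulting misclassification would differ between arms, and a larger sample would not remove it. The outcome is not a minor one: aim ii names the excess risk of further fracture over 2 years, and the Sample size section treats further fracture as the adverse event of most interest and gives a power statement for it.

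**Working it through.** **1. The statements side by side**

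| Element | Vertebroplasty | Placebo |
|---|---|---|
| Needle end point | vertebral body | lamina |
| Material left | about 3–4 ml opacified PMMA | none |
| Films at 12 and 24 months | thoracic and lumbosacral | thoracic and lumbosacral |
| Already fractured level graded | yes | yes |

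The second row gives a visible marker that separates the arms. The third and fourth rows mean that the readers are required to look at it. Withholding the allocation list does not remove the marker. A second independent reader does not help either, because both readers see the same cue.

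**2. The plan's own fracture figure**

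Stated: 82 per group, 80% power, 3-fold excess, two-sided α = 0.05, log-rank test. The control risk used is not named. I assume 10%, the figure the section gives for patients on osteoporosis treatment.

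- Vertebroplasty risk at a hazard ratio of 3: 1 − 0.9³ = 0.271.
- Expected events: 164 × (0.10 + 0.271)/2 = 30.4.
- Freedman: power = Φ(√30.4 × (3 − 1)/(3 + 1) − 1.96) = 78.8%.
- Schoenfeld, same inputs: 85.8%.

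The stated 80% lies between the two, so the figure is reproduced and is not in dispute.

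**3. Illustration of over-calling when there is no true effect**

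Assumptions, none of them from the document except the 10%: true risk 10% in both arms; readers over-call in a fraction x of fracture-free cemented patients; no over-calling in the placebo arm.

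Observed risk in the vertebroplasty arm = 0.10 + 0.90x.

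| x | Observed risk | Risk ratio against 0.10 |
|---|---|---|
| 2% | 0.118 | 1.18 |
| 3% | 0.127 | 1.27 |
| 5% | 0.145 | 1.45 |

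For false rejection with 82 per arm, I use a two-proportion normal approximation, with a and b the two observed risks, d = b − a and p̄ = (a + b)/2:

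Φ((d − 1.96·s₀)/s₁) + Φ((−d − 1.96·s₀)/s₁), with s₀ = √(2p̄(1 − p̄)/82) and s₁ = √((a(1 − a) + b(1 − b))/82).

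At x = 5%, d = 0.045, p̄ = 0.1225, s₀ = 0.0512 and s₁ = 0.0511, which gives 0.141. At x = 2% the result is 0.066. The nominal level is 0.05.

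**4. Illustration of under-calling when there is a true effect**

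Take true risks of 10% and 30%, with a fraction m of true vertebroplasty fractures missed and none missed in the placebo arm. The same approximation gives:

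| m | Observed risk | Risk ratio | Power |
|---|---|---|---|
| 0% | 0.30 | 3.0 | 90% |
| 10% | 0.27 | 2.7 | 81% |
| 20% | 0.24 | 2.4 | 67% |
| 30% | 0.21 | 2.1 | 49% |

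Under-calling shrinks a 3-fold excess, but substantial loss of power needs a substantial share of fractures to be missed.

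**The case against.** The best case for the plan has five parts.

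**A condensed article.** Film handling often sits in a full protocol or imaging manual that is not shown, so the absence of a described masking step proves little. That is fair as far as it goes. The point rests on something else: the article positively claims blinded readers while its own endpoint makes them grade the cemented vertebra. Hidden procedural detail cannot reconcile those two statements unless the endpoint is split.

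**What blinded means.** It may mean only that readers lack the allocation list and clinical data. That would be a true statement, but it does not conceal the arm, and the article does not limit its claim in that way.

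**Safeguards in the grading.** There is a height-loss equivalence of more than 15%, a comparison with baseline, and a second independent reader. These limit discretion without removing it.

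**Small effect beside the target.** Risk ratios of 1.18 to 1.45 are well below the 3-fold excess the trial is sized for, and the article says it is not designed for small differences. This stands, and it limits how much weight the illustration can carry.

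**Inherent to the treatment.** Cement will always be visible, and pain, quality of life, disability and the Up and Go test do not depend on the film readers. This also stands.

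Some stronger readings are tempting. A reader might infer that every single follow-up film gives the arm away; one thoracic or lumbar view may miss the treated level, and it is the patient's set that reveals it. A reader might infer that fractures will be over-called; the Background also reports that the two controlled before-after studies conflicted, and nothing fixes the direction. A reader might infer that a few per cent of under-calling would hide a real excess; the last table in the working does not support that.

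**Conclusion.** The claim of blinded fracture reading does not hold as written. The article's own description of the two procedures, the films and the endpoint means that a patient's film set can show the arm. The defect is confined to the radiographic fracture outcome at 12 and 24 months, a secondary safety outcome but the one aim ii singles out. It does not reach the 3-month pain primary, and it would be wrong to read it as a failure of the trial's blinding as a whole.

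That the readers can see the arm follows from the text. That they would be biased by it does not, and neither the direction nor the size can be established. The risk ratios of 1.18, 1.27 and 1.45, and false rejection of about 7% and 14% at 2% and 5% over-calling, rest on assumed reader behaviour and a 10% risk in both arms. They show only that modest over-calling could be enough to matter.

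**What to change.** 1. **Correct the claim.** State that the readers are blind to the allocation list and clinical data, but cannot be blind to arm where cement is visible.
2. **Split the endpoint** under Outcome Assessment into new fractures at non-index levels and progression at index levels. Say which of these the fracture power statement refers to.
3. **Mask where feasible.** Cover the index level or levels on baseline and follow-up films with the same fixed margin in both arms. Do not extend the mask where cement has leaked: that could happen only in the vertebroplasty arm, so it would itself reveal the arm and would make adjacent levels harder to grade in that arm alone. Grade and lock the non-index levels first. Then read the index levels as a declared-unblinded assessment.
4. **Flag as unblinded** any read where cement remains visible outside the mask.

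The change needs to be in place before films are read, since grades made with cement in view can be made blind only by a re-read.

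The cost is a small masking step by a person who does not read the films, and a second pass by the same readers for the index levels. No extra film, visit or reader is needed. Index-level progression will be reported separately as unblinded, and some unblinding will remain where cement has leaked.

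### The new-fracture definition counts progression of the index vertebra, which is cemented in one arm only, so the safety comparison can dilute or mask an excess of fractures at untreated levels

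*Protocol article*

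**What the plan says.** In the protocol article, Outcome Assessment gives the rule in two limbs. First: "A new vertebral fracture will be defined as an increase in deformity grade (equivalent to a decrease of >15% in any vertebral height"), measured against the baseline film. Second: "or a new fracture in an existing prevalent fracture if there is progression to a higher grade of deformity". Neither limb sets the index level aside, and no separate count at untreated or adjacent levels is named.

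Under Participants, entry is limited as follows: "Only participants with one or two recent vertebral fractures, defined as vertebral collapse and oedema or fracture line". The index vertebra is thus a prevalent fracture in everyone. The only limit on its degree of collapse is the exclusion of "osteoporotic vertebral collapse of > 90"%, so many index vertebrae still have room to lose height.

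Under Interventions, the active arm has cement injected into the fractured vertebral body, while in the placebo arm the injection is simulated. The Background states: "Treated vertebrae have been found to be stronger and stiffer after vertebroplasty compared to osteoporotic bone". It describes the feared harm as subsequent fracture, particularly next to treated levels. Aim ii is the excess risk of further fracture over 2 years.

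**The concern.** The intervention acts mechanically on one component of its own safety endpoint, in one randomised arm only. If cement limits further collapse of the vertebra it fills, the placebo arm collects index-level events that the active arm is partly spared. Those events are added to fractures elsewhere in the spine, which is where the article locates the suspected harm. The two effects then pull in opposite directions within one count.

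What is at stake is the reading of aim ii. The Sample size section calls further vertebral fracture possibly the most relevant adverse event and claims adequate power for medium to large excesses. A null result on the pooled count could hide a real excess at untreated levels, and the error would run towards reassurance.

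**Working it through.** **Inputs from the article (Sample size).** 82 per arm, two-sided alpha 0.05, log-rank test, 3-fold excess, 80% power. The one-year control risk is about 10% with osteoporosis treatment and about 20% without.

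**Reproducing the stated power.** The article does not say which control risk it used. A 10% control risk with a hazard ratio (HR) of 3 gives an active-arm risk of 1 − 0.9³ = 27.1%. Two proportions, 82 per arm:

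- difference × √82 = 0.171 × 9.055 = 1.548
- 1.96 × √(2 × 0.1855 × 0.8145) = 1.077
- √(0.1 × 0.9 + 0.271 × 0.729) = 0.536
- (1.548 − 1.077)/0.536 = 0.88, so power is 81.0%

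Freedman's log-rank formula gives 78.8% and Schoenfeld's 85.8%. The stated 80% is reproduced on this reading. Reading the 3-fold excess as a risk ratio (10% v 30%) would need only 62 per arm, which fits less well.

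**Adding the index level.** Let q be the placebo-arm risk of index progression over the same period, and f × q the risk in the active arm (f = 0 full protection, f = 1 none). Neither is in the article; both are assumptions. Taking index and other-level events as independent:

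- placebo risk = 1 − 0.9 × (1 − q)
- active risk = 1 − 0.729 × (1 − f × q)
- HR = ln(1 − active risk)/ln(1 − placebo risk)

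Example, f = 0 and q = 10%: placebo 1 − 0.9 × 0.9 = 19.0%, active 27.1%, HR = ln 0.729/ln 0.81 = 1.50.

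| Protection | q | Placebo v active | HR | Power (two proportions) |
|---|---|---|---|---|
| Index level not counted | – | 10.0% v 27.1% | 3.00 | 81% |
| Full (f = 0) | 5% | 14.5% v 27.1% | 2.02 | 51% |
| Full | 10% | 19.0% v 27.1% | 1.50 | 23% |
| Full | 15% | 23.5% v 27.1% | 1.18 | 8% |
| Full | 25% | 32.5% v 27.1% | 0.80 | reversed |
| Half (f = 0.5) | 5% | 14.5% v 28.9% | 2.18 | 61% |
| Half | 10% | 19.0% v 30.7% | 1.74 | 41% |
| Half | 20% | 28.0% v 34.4% | 1.28 | 14% |
| None (f = 1) | 10% | 19.0% v 34.4% | 2.00 | 61% |

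**Where the excess cancels.** With full protection, 0.9 × (1 − q) = 0.729 gives q = 19%. For 10% v 30% the same equation gives 22%; for a 2-fold excess (10% v 20%) it gives 11%. With half protection and a true HR of 3, the HR is 1.04 at q = 30% and 0.88 at q = 40%, so reversal lies between those. With no protection both arms are multiplied by the same (1 − q), so the order cannot reverse.

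**The case against.** The strongest case on the other side has five parts.

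1. *The article does not say that cement prevents collapse.* This stands. It reports greater strength and stiffness, and elsewhere attributes restored strength to post-mortem work. A reader might infer that the comparison is biased in favour of vertebroplasty, or that its sign will flip. The article supports neither: it gives no progression rate and no clinical protective effect, and reversal needs high progression together with strong protection. Positive correlation between index and other-level events would also shrink the distortion.

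2. *The pooled count is a legitimate net measure of further fracture.* This stands in part. Aim ii is not worded as untreated levels only, and the rule is formally the same in both arms. But a net count cannot show whether harm elsewhere is being offset at the treated level. Outcome Assessment itself separates treated from untreated vertebrae when it explains why films are taken.

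3. *Levels can be split at analysis, and an analysis plan may say so.* No data would be lost, because readers grade each vertebra. The article nevertheless fixes a definition, and as worded it includes the index level.

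4. *Year-by-year risk.* Setting "from the baseline radiograph to the end of the study" beside "It will quantify the risk of developing new vertebral fractures in the first and second year following vertebroplasty", a reader might infer that first-year and second-year fractures cannot be separated. They can: films are required at both 12 and 24 months to determine incidence. The wording is loose but does not remove the 12-month reading.

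5. *Age of the baseline film.* From "If not already available, plain films of the thoracic and lumbosacral spine will be obtained" a reader might infer that a film of any age would serve, so that pre-procedure fractures are counted. The Participants section largely bounds this: radiographs must confirm the fracture, pain may have lasted at most 12 months, and MRI (or CT plus bone scan) assesses whether the fracture is recent.

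**Conclusion.** The point holds as a defect in the endpoint definition. Index-level progression is counted as new fracture, and the index vertebra is mechanically altered in one arm only. Dilution needs no protective effect at all: 10% progression with f = 1 already takes the HR from 3 to 2.0 and power from 81% to about 61%. With full protection the same 10% leaves an HR of 1.5 and about 23% power, and about 19% progression removes the excess.

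These figures rest on assumed values of q and f, on independence of events within a patient, and on the 10% control risk that reproduces the stated power. They show what the rule permits, not what will happen. An index vertebra already in the highest deformity grade cannot progress further, which lowers q. Fracture is not the primary outcome, which is overall pain at 3 months, so the efficacy conclusion is untouched. The point bears on the safety half of aim ii.

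**What to change.** Define the safety endpoint as at least one new or worsened fracture at a vertebra that was not an index level, whether treated or sham-treated, with the same grading rule in both arms. Name adjacent levels as a subset. Report index-level progression separately by arm, and give the all-level count as a supplementary result so that the net burden remains visible.

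The cost is a rewording: the films, the blinded double reading and the per-vertebra grading are already planned. The downside is somewhat fewer counted events. If the 10% control risk is taken to describe non-index levels, power at 82 per arm stays at about 79% to 86% depending on the formula.
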